**Conclusion::**

This study data will inform a larger, multi-centre study exploring further
the interplay between frailty, biomarkers and arterial stiffness
parameters.

## Introduction

As the world’s population keeps ageing, a corresponding increase in older adults with
frailty occur.^1^ In the UK, it is estimated that close to a fifth (18%) of the
population are 65 years and over, out of which 7% are known to be severely
frail.^2,3^
Indeed, the House of Lords report, considers healthy ageing as one of the 4 cross
cutting ‘grand challenges’ in the UK,^4^ thus emphasising the importance
of addressing matters related to ageing and frailty.

Frailty as a geriatric syndrome, is associated with an increased risk of adverse
outcomes,^5,6^
such as falls, reduced mobility and independence, increased hospitalisations,
cognitive decline, disability and death.^7^ It is known to be a risk factor
of cardiovascular disease and when coupled with arterial stiffness, potentiates this
risk.^8,9^ The association
between frailty and arterial stiffness is well known.^8,10^ In a cross-sectional study
involving 2171 community-dwelling participants aged 60 years and over, arterial
stiffness was noted to be strongly associated with pre-frail and frail
status.^11^ Although this association exists, arterial stiffness does not
uniformly correlates with the various stages of frailty^12-14^ though it is considered to be
the hall mark of vascular ageing.^8^

In the mechanism of vascular ageing, inflammation and oxidative stress have been
observed as predominant underlying factors aside others such as genomic
instability.^15-17^ Studies have
shown strong association between oxidative stress and inflammation with
frailty.^18-21^ Two oxidative biomarkers
malondialdehyde (MDA) and protein carbonylation were noted to have strong
association with frail elderly people in 742 adults studied, compared to the
pre-frail and non-frail.^22^ In a prevalent-case control study of 55 adults greater than
65 years, compared to healthy controls, frail adults had a higher percentage of
circulating 8-isoprostane (*P* = .001), a validated oxidative stress
marker.^23^ A significant increase in 8-hydroxy-2’-deoxyguanosine (8-OHdG)
and 8-isoprostane levels, together with higher levels of interleukin-6, were noted
to be present in the prefrail and frail elderly adults in contrast to the non-frail
in a study of 140 patients with Alzheimer’s.^24^ Similarly, another study in
2019 examining the relationship between inflammation and frailty among 817 adults 65
years and older, showed 2 inflammatory markers (Erythrocyte sedimentation rate-ESR
and Neutrophil to lymphocyte ratio-NLR) to be significantly elevated in the frail
group compared to the non-frail groups.^25^ In a systematic review with
meta-analysis on the association of inflammatory biomarkers and frailty, there was a
strong association between these markers (Interlukin-6 – IL-6, and C-reactive
protein – CRP) and frailty status (pre-frail and frail), a proof of the role of
inflammation in frailty.^26^

Although oxidative stress and inflammaging (the chronic state of inflammation in
ageing) are known to be associated with frailty and considered to be underlying
vascular ageing, there are no observational studies in human, on the effects of
these 3 on frailty. Frailty is thought to be potentially reversible especially in
its early stages.^27-34^ Therefore, its early
detection and management is key to prevent and reduce its impact on older
adults.^26,35,36^ Thus, a major rationale for this pilot study is to be able to
offer an objective measure based on arterial stiffness for frailty, incorporating
the roles oxidative stress and inflammation play.

This would help ultimately in the early detection of frailty, and subsequently
contribute to the body of evidence-based medicine where clinicians may in the
medium-to-long term, use these bio-markers to help assess degrees of frailty, and
aid in slowing down progression of frailty, by addressing issues of inflammation and
oxidative stress.

### Study aim

To study the mediating roles of oxidative stress, inflammation and arterial
stiffness in the pathogenesis of frailty.

### Study objective

To undertake a pilot study exploring the use of markers of inflammation,
oxidative stress and arterial stiffness as an objective measure for frailty.

### Hypotheses

Frail older adults with arterial stiffness have a corresponding increase in
biomarkers of oxidative stress and inflammation.

Research Question:

Is oxidative stress and inflammation associated with arterial stiffness in frail
older people?

## Study Design

This is an observational longitudinal cohort study looking at the association between
oxidative stress and inflammation among older adults with varying frailty status and
arterial stiffness over a period of 6 months. The main goal of this pilot study is
to provide preliminary data to inform a follow-up larger, national, multi-centre
study exploring further the links between frailty and vascular parameters.

## Study Methods: Participants, Interventions and Outcomes

### Study setting

The study will be undertaken at the University Hospitals Sussex NHS Foundation
Trust, Clinical Research Facility (CRF). Participants will be invited for
recruitment from outpatients at University Hospitals Sussex NHS Trust.

### Eligibility criteria

Inclusion criteria:

Age 70 years and above with a Clinical Frailty score ⩽6/Electronic
Frailty Index ⩽0.36.Patients who have capacity to give informed consent.

Exclusion criteria:

Malignancy, with current active treatmentPatient unable to give informed consentPatient with a Rockwood Frailty score 7 to 9 or Electronic Frailty Index
in the severe frailty group (>0.36).

Should a participant loose capacity during the study, they will be excluded from
further involvement in the study, however the data collected up until the time
of loss of capacity will be used. Initially, capacity to participate in the
study will be assessed prior to consent by a member of the research team, and
again by the research team member over the phone prior to the study visit.

### Measurements

At recruitment and at follow up, frailty status of participants would be assessed
using the Rockwood/Clinical Frailty score (CFS) and the electronic Frailty index
(eFI) score. The Rockwood/CFS is a frailty assessment spectrum grouped from 1
(very fit) to 9 (terminally ill). The electronic frailty index (eFI) classifies
frailty into 4 groups spanning from fit (eFI < 0.12) to severely frail (eFI
> 0.36). Participants in this study, would be categorised based on their
scores as no-mild frailty (CFS ⩽ 3, eFI ⩽ 0.24) and moderate frailty (CFS 4-6,
eFI 0.24-0.36). The choice of stratifying the study participants into a spectrum
of frailty states from not-frail to mildly frail and moderately frail is based
on the knowledge that progression towards advanced frailty states can be delayed
and/ or reversed if the right intervention is implemented.^31,33,37^

Arterial stiffness will be measured in 2 ways: using Complior^®38^ and
CAVI^®.39^ Assessment of arterial stiffness will be done at room
temperature with the patient supine and after having rested for 10 minutes.
Patients will be asked to refrain from smoking, eating or drinking caffeinated
drinks for 3 hours before measurements and to avoid consuming alcohol for 10
hours before measurements. Participants will be offered reimbursement for travel
expenses.

(a) The Complior^®^ is a non-invasive device which measures Pulse Wave
Velocity and central pressures. The carotid, femoral and radial pulses are
palpated and marked, and measurements are taken between them. The wave forms are
then measured and recorded on the Complior^®^ programme using small
sensors. We will perform at least 2 measurements, and if similar will use the
mean of these. If these differ by more than 0.5 m/s, a third measurement will be
performed. The PWV value should be the median of these measurements.

(b) Cardio-Ankle Vascular Index (CAVI^®^) is another index which
assesses arterial stiffness, this time it uses measurements in all 4 limbs.
CAVI^®^ then equates the stiffness using the pulse wave between the
heart and the ankles. Complior and CAVI measurements will be done by the same
person to ensure consistency. These 2 measurements will be done only once at
baseline and not at follow up since we do not expect any changes within 6
months.

(c) A blood sample will be obtained by a trained research nurse or doctor. The
participant will be asked to give approximately 20 mls of blood (one and a half
tablespoons), plasma samples will then be stored at −80°C until they are tested.
All participants will have samples taken to measure markers of oxidative stress
and inflammation in the clinical research laboratory at the University of
Sussex. Inflammatory markers to be measured would include high sensitivity
C-reactive protein (hs-CRP) and Interlukin-6 (IL-6). Markers for oxidative
stress to be measured would include nitrotyrosine (NT) and
8-hydroxy-2’-deoxyguanosin (8-oxo-dG). Inflammation and oxidation profiles will
be measured by ELISA using commercially available assay kits. Samples would be
handled by the research nurse or doctor for storage before being transported to
the research laboratory at the University of Sussex to be assayed together.

(d) Other biochemistry measurements would be recorded from the hospital computer
system which would include lipid profile, thyroid function and full blood count.
Other routine clinical observations to be checked would be blood pressure, body
mass index (BMI) and random blood sugar (RBS).

(e) At recruitment and follow up, cognition of participants would be assessed
using the Abbreviated Mental Test Score (AMTS) and Montreal Cognitive Assessment
(MoCA). These readings would be taken from the patients’ file. Patients with
scores less than 8 on the AMTS and 23 on MOCA will be excluded from the
study.

(f) Measures of frailty to be assessed will include hand grip strength using the
hand dynamometer, timed up and go test (TUGT) and body impedance with the
Tanita.

(g) Participants will be followed up at 6 months for second measurements to be
taken. Prior to follow up visit, participants would be contacted via telephone
call for booking of appointment. All measurements taken during
baseline/recruitment would be repeated except for the arterial stiffness. Snacks
will be provided for the participants after their participation both at
recruitment and follow up and their transportation bill catered for.

### Sample size

This is a pilot study with no formal sample size calculation done. We aim to
recruit 40 participants who fit the eligibility criteria, but this number will
be adjusted upwards to 50 participants to account for an expected dropout rate
of 20%. We aim to recruit at least 2 participants per week within 5 months. The
selected sample size is considered reasonable for a pilot/feasibility study by
NIHR.^40,41^ Similarly, this is in line with Browne’s rule of thumb
for pilot study sample size calculations which recommends at least 30 subjects
for pilot studies to estimate differences between 2 groups.^42^ It is
further supported by Julious^43^ who suggests that a
minimum of 12 subjects per treatment arm /group is relevant to reduce
imprecision around the estimates of a standard deviation. The chosen sample size
of 50 is a pragmatic approach considering previous studies which used similar
numbers, where 28 frail older adults were compared with 27 robust non-frail
older adults assessing the differences in oxidative stress markers between both
groups.^23^ Participants would be stratified into 2 groups based on
their frailty status as group 1 having no-mild frailty (ie, having a Rockwood
frailty score ⩽3) and group 2 made up of moderate frailty with a Rockwood
frailty score >3 in line with the study’s inclusion criteria. We would aim to
have an equal number of 25 participants in each group.

### Recruitment and obtaining consent

Potential participants for the study will be highlighted to the research team by
clinical staff within the hospital. Most of these potential participants will be
identified on the care of the elderly wards and clinics. The potential
participants will be invited to listen to an initial explanation of the study
and asked if they would like to be considered as a participant, at this stage a
participant information sheet (PIS) will be provided. This will happen whilst
the potential participant is in hospital. Interested individuals will be advised
to spend at least 24 hours considering involvement in the study. Following at
least 24 hours, interested individuals will discuss the study again and any
questions will be answered by a trained member of the research team. If the
person wishes to be involved, an appointment will be made at which time formal
written consent will be given prior to assessment. An appointment will be made
for the follow up visit in 6 months post discharge. Participants transport fares
would be catered for by the team.

Should a participant loose capacity during the study, they will be excluded from
further involvement in the study, however the data collected up until the time
of loss of capacity will be used.

## Data Collection, Management and Analysis

### Assessment and collection of outcome, baseline and other study data

The research staff performing assessments of arterial stiffness will be trained
and validated in the approved methods of using the various pieces of equipment.
The following machines are being used to assess arterial stiffness and the
corresponding links to information on validity and reliability are provided.

Complior^®^: http://www.complior.com/info-center^44^CAVI^®^: http://www.fukuda.co.jp/english/products/special_features/vasera/cavi.html^45^

Participants will be followed up at 6 months following the initial study visit.
Prior to follow up visit, research staff will check if the participant is
currently in hospital or if the participant is deceased. In the unlikely event
that the participant has died or that they are currently an inpatient, the
follow-up telephone call will not be made. Participants will be asked to provide
an email address if they would like to be contacted via email to arrange the
timing of the follow-up visit.

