### Statistical analysis plan

Results will be imported into STATA for data cleaning and statistical analysis.
Since this is a pilot study, analysis will be mainly descriptive. Descriptive
statistics for continuous data will be assessed using means and standard
deviations for normally distributed variables, or medians and interquartile
ranges for skewed continuous variables. Analysis would involve looking at
missing data, drop- out rate which would inform sample size calculation for a
future larger study. Categorical data will be summarised using frequencies and
percentages and comparison between the 2 groups (moderate frailty and no-mild
frailty) done using the chi-squared or Fishers exact test.

Where data are not normally distributed these will be log transformed and
presented as geometric means with their 95% confidence interval. Where data are
not normally distributed even after transformation, these will be presented as
median (IQR) and comparisons between groups done using the Wilcoxon rank-sum
test.

The Primary outcome (change in frailty status) will be compared between the 2
groups using the 2-sample independent t test or a simple linear regression.
Other outcome measures will be analysed in a similar way except if these are
skewed when the Wilcoxon rank-sum test will be used. Similarly, a linear mixed
models approach will be used to study the 2 study time points (baseline and
follow up) in the 2 groups. All tests will be 2 sided and significance will be
set at *P* < .05.

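### No deferred 6-month visit is stated for inpatients, and loss of capacity (and, as worded, a low cognitive score) ends follow-up, so a selected share of those who worsened is likely to be missing from the primary outcome

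*Protocol article*

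**What the plan says.** All references are to the protocol article.

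- **Outcome.** Statistical analysis plan: "The Primary outcome (change in frailty status) will be compared between the 2" frailty groups, by a two-sample t test or simple linear regression. A mixed model on the two time points is added. Measurements: "At recruitment and at follow up, frailty status of participants would be assessed", using the CFS and the eFI.
- **Death or admission.** Assessment and collection of outcome, baseline and other study data: "In the unlikely event that the participant has died or that they are currently an inpatient, the follow-up telephone call will not be made". Measurements, item (g), gives the purpose of the call, which is to make the follow-up appointment.
- **Loss of capacity.** Eligibility criteria: "Should a participant loose capacity during the study, they will be excluded from further involvement in the study". Data collected before that point are kept. The recruitment section repeats the rule.
- **Cognition.** Measurements, item (e), has AMTS and MoCA assessed at recruitment and at follow-up, and then states: "Patients with scores less than 8 on the AMTS and 23 on MOCA will be excluded from the study". These cut-offs do not appear in the list of exclusion criteria.
- **Missing data.** The analysis plan will look at missing data and the dropout rate, to inform the sample size of a later study. The Sample size section expects 20% dropout.
- **Background.** The Introduction lists adverse outcomes of frailty, "such as falls, reduced mobility and independence, increased hospitalisations", followed by cognitive decline, disability and death.

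**The concern.** The events that stop a participant from being measured at 6 months are largely the events that the article itself attributes to frailty. A person admitted on the day of the check, or who has lost capacity, keeps a baseline value but has no change score. If these people worsened more than those who were seen, the 6-month change is missing not at random.

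The admission route is the most avoidable. A short stay at the wrong moment is enough to trigger the no-call rule, and nothing says that the call is made later. The article calls death or admission unlikely. Yet participants are at least 70 years old, have a CFS of up to 6, and are mostly identified on elderly-care wards and clinics.

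At stake is the frailty change that the pilot hands to the planned multi-centre study. If it is understated, that study is planned on too low a rate of progression.

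**Working it through.** **1. The plan's own figure.** Recruitment target = 40 / (1 − 0.20) = 50, as stated. This allowance protects the number of completers. It does not make them representative.

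**2. Following the stated rules to the change score.**

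| Event before 6 months | Stated rule | Change score |
|---|---|---|
| Inpatient when checked | No call; no deferral given | Missing unless a visit is arranged by another route |
| Death | No call | Cannot exist |
| Loss of capacity | Participation ends, earlier data kept | Missing |
| Low AMTS or MoCA at follow-up | Excluded, if the wording is applied at both times | Removed |
| Worsened, but outpatient, with capacity and above the cut-offs | Seen as planned | Present |

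The last row matters: many who worsen are still measured.

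**3. Do the planned analyses repair this?** The t test or regression on change uses completers. The mixed model can keep people with a baseline value only, but it assumes that, given the observed data, loss does not depend on the unseen 6-month value. Admission, cognitive decline and death are likely to be related to that value.

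**4. Possible size for a proportion. All rates are assumed; the documents give none.** Let p be the true share who progress, a the share of progressors lost, and b the share of non-progressors lost. Then:

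observed share = p(1 − a) / [p(1 − a) + (1 − p)(1 − b)]

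Take p = 20% in the no-mild group and 40% in the moderate group, a true difference of 20 points.

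- a = b = 20%: observed 20% and 40%. No bias.
- a = 40%, b = 10%: 0.12/0.84 = 14.3% and 0.24/0.78 = 30.8%. Difference 16.5 points. Overall loss (16% + 22%)/2 = 19%.
- a = 60%, b = 5%: 0.08/0.84 = 9.5% and 0.16/0.73 = 21.9%. Difference 12.4 points. Overall loss (16% + 27%)/2 = 21.5%.

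Overall loss stays close to the planned 20% throughout. Only its distribution changes.

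**5. Possible size for a mean CFS change, also assumed.** Take 25 per group, completers' mean change 0.1 (no-mild) and 0.3 (moderate), observed difference 0.2, and 10 losses in all.

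- Losses 2 and 8, each lost person worse by 1 point: (23×0.1 + 2×1)/25 = 0.172 and (17×0.3 + 8×1)/25 = 0.524. Full-cohort difference 0.352.
- The same split, each worse by 3 points: (2.3 + 6)/25 = 0.332 and (5.1 + 24)/25 = 1.164. Difference 0.832.
- Losses 5 and 5, each worse by 1 point: (20×0.1 + 5×1)/25 = 0.28 and (20×0.3 + 5×1)/25 = 0.44. Difference 0.16.

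In all three cases progression is understated within each group. The observed between-group difference of 0.2 is too small under the uneven split and slightly too large under the even one.

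**The case against.** The strongest reply has five parts.

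- **The text withholds a telephone call, not the visit.** The same section offers email contact for arranging the visit, and the recruitment section mentions a follow-up appointment. That stands, so a reader who infers that every inpatient is lost goes beyond the text. Still, neither route is tied to inpatients and no later assessment is stated.
- **The cognitive cut-offs are probably entry criteria put in the wrong section.** Their wording resembles the exclusion list more than the rule for participants who lose capacity. This is the likelier intention, but the sentence follows one that places the assessment at both times and sets no limit.
- **A dead participant cannot attend, and ending participation on loss of capacity follows from consent.** This stands fully. Neither rule is a design error in itself; the gap is that the outcome takes no account of these losses.
- **Missing-data methods are commonly left to an analysis plan that is not shown.** Also fair: the absence of a sensitivity analysis would not be a finding alone. The point rests on follow-up rules that the article does state.
- **This is a mainly descriptive pilot, and stiffness is measured only at baseline.** Baseline associations between markers and stiffness are unaffected. Change in frailty, however, is the named primary outcome and is meant to inform a larger study.

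A reader might also infer that those who progressed are missing altogether, or that the group contrast must shrink. The documents support neither. Progressors who remain outpatients with capacity are measured, admission on one day is not the same as progression, and the article does not say in which group losses will fall.

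**Conclusion.** The concern holds as stated in the heading. The inpatient rule and the capacity rule are in the text. The cognitive route depends on reading an ambiguous sentence literally. Together they make it likely that loss at 6 months is related to worsening, so progression is probably understated, and the planned analyses do not correct for that.

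The size is unknown. With loss near the planned 20%, the illustrations run from no bias (loss unrelated to progression) to an observed 21.9% in place of a true 40% in the moderate group. All of these rest on assumed progression and loss rates. No claim is made about the direction of between-group bias.

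**What to change.** 1. **Inpatients.** State that the call and visit are deferred until after discharge, within a stated window, and that the actual interval from baseline is recorded.
2. **Cognitive cut-offs.** State that AMTS and MoCA cut-offs apply once, at entry. List them with the exclusion criteria, and say that no one is removed for a follow-up score. The separate capacity rule is unchanged.
3. **Analysis.** Keep the planned primary analysis. Add one sensitivity analysis in which deaths and capacity losses count as worsened. It can use worsened yes/no by group with the chi-squared or Fisher's exact test that the plan already names. Counting a death as worsened is one of several defensible choices, which is why it belongs in a sensitivity analysis.
4. **Reporting.** Give reasons for loss by frailty group: death, admission, loss of capacity, withdrawal, other.

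**Cost.** Protocol wording, a small amount of extra analysis, and a few visits later than 6 months. Staff already check for death and admission, so no new procedure is needed and the target stays at 50.
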